To understand the impact of PrEP policies and programs (objective 2), we will leverage the legal coding and health jurisdiction program provision datasets described above to conduct quasi-experiments with outcomes of PrEP starts, PnR, and retention in care. PrEP programs have been adopted by local health authorities in the context of the disbursement of EHE funds as grants to applicants. Despite the lack of random assignment of jurisdictions to policies and programs, we propose a quasi-experimental design that allows us to have findings that reflect several of the characteristics of randomized studies, including temporality and controlling for time-invariant factors. Although quasi-experimental approaches are subject to some limitations inherent to nonrandomized designs such as challenges in controlling for time-varying characteristics, these designs minimize bias relative to other analysis approaches. Moreover, quasi-experimental approaches improve upon the external validity of randomized studies because the data stem from programs that have been enacted in practice. Because of the study design, results will be well positioned to inform real-world programs such as those that comprise EHE efforts. For quasi-experiments, we will conduct analyses using methods such as difference-in-differences (DID) that account for intervention and control jurisdiction trends before program implementation. Because interventions are implemented at different points in time, we will use the heterogeneous DID method proposed by Callaway and Sant’Anna [32] or a similar method to account for potential confounding from multiple implementation periods. Health jurisdictions implementing a program or policy will be the primary intervention unit, and controls will be jurisdictions not implementing a program. DID analyses will be accomplished with regressions that include a term for group (eg, telemedicine PrEP program or not), period (month), and group-by-period interactions that serve to estimate the effect of the intervention. Our approach provides a relatively large sample size for such analyses, with many of the 50 counties or local jurisdictions funded under the EHE program implementing programs under assessment, and other non-EHE jurisdictions also implementing some of the identified programs. Control jurisdictions will be counties or states in the United States that do not implement a particular program, using 9 years of monthly PrEP use data (2016-2024). Depending on characteristics of the intervention, such as statewide provision, we may restrict the control group to jurisdictions meeting certain criteria in order to improve the match between intervention and control groups. For instance, we might match counties by HIV prevalence or jurisdiction size.

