
#### Power Calculation: Objective 2

The study design achieves 90% power to detect a minimum difference between intervention and control county PrEP rate means of 2.4 PrEP starts per 100,000 population. This is based on a sample size of 8,784,000 county-person-month observations, a figure obtained from a minimum estimate of 6 counties implementing a particular program and 238 control counties not implementing the program. We assume that each county has an average of 300 individual PrEP users (a conservative estimate because the 2021 average and median county PrEP users are 1210 and 482), and we assume an average of 60 months of follow-up (a conservative estimate because the total follow-up period is 144 months). The standard deviation of PrEP use at the county level is 73, and we conservatively assumed a small (0.05) within-person correlation. The power assessment is based on a time-by-treatment interaction test using a mixed-model analysis with a significance of 0.05. We performed a similar analysis for state-level policies and found a minimum detectable difference of <3 additional PrEP starts. Power calculations were performed in PASS 2022.

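### The 2.4 minimum detectable difference reproduces as the month-60 gap of a linear slope test, so 90% power is not established for the planned difference-in-differences analysis

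*Protocol article*

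**What the plan says.** Under Power Calculation: Objective 2, the Protocol article reports "90% power to detect a minimum difference between intervention and control county PrEP rate means of 2.4 PrEP starts per 100,000 population". The total is introduced with "This is based on a sample size of 8,784,000 county-person-month observations", built from "a minimum estimate of 6 counties implementing a particular program and 238 control counties not implementing the program", with 300 users per county and 60 months. The SD is 73, described as county-level; the within-person correlation is 0.05, described as a conservative choice. On the test: "The power assessment is based on a time-by-treatment interaction test using a mixed-model analysis with a significance of 0.05".

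Under Data Analyses, Objective 2 is to be analysed differently: "we will use the heterogeneous DID method proposed by Callaway and Sant’Anna [32] or a similar method to account for potential confounding from multiple implementation". The regressions are described as having a group term, "period (month), and group-by-period interactions that serve to estimate the effect of the intervention". No base period and no split of the 60 months into pre-start and post-start months is given.

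The Limitations section relies on the power calculation to say that enough data would remain if EHE funding stopped.

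**The concern.** The paragraph names one quantity (a difference in means) and one test (a time-by-treatment interaction), while the analysis section plans another estimator. If 2.4 belongs to a slope test, it is not the smallest average program effect that the DID can detect.

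This is the only power statement for the main causal objective. A reader of a null result would take 2.4 as the effect that the study could have excluded. Objective 3 models the programs that Objective 2 finds effective, so a null from an analysis with unknown power could drop a useful program.

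**Working it through.** **Inputs** (Power Calculation: Objective 2): 6 × 300 = 1,800 intervention persons; 238 × 300 = 71,400 control persons; m = 60 months; SD = 73; ρ = 0.05; α = 0.05; power 90%. Assumptions: two-sided test (not stated; one-sided gives 94.2% power at 2.4 and does not reproduce the claim), equal correlation between all months, normal approximation.

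K = 1/1,800 + 1/71,400 = 0.0005696, √K = 0.02387. z = 1.960 + 1.282 = 3.242. MDD below means minimum detectable difference at 90% power.

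**1. The plan's figure, as a slope difference.** Sxx = m(m² − 1)/12 = 60 × 3,599/12 = 17,995.
SE of the month-60 gap = 59 × 73 × √(0.95/17,995) × 0.02387 = 0.747.
MDD = 3.242 × 0.747 = 2.42; power at 2.4 = 89.5%. This reproduces the printed figure. Lines that start together and end 2.4 apart average 2.4/2 = 1.2 apart.

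**2. The same inputs, as a time-averaged difference in means.**
MDD = 3.242 × 73 × √[(1 + 59 × 0.05) × K/60] = 1.45, not 2.4.

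**3. Check on the word conservative.** Raising ρ from 0.05 to 0.5 lowers the slope MDD from 2.42 to 2.42 × √(0.50/0.95) = 1.76, but raises the means MDD from 1.45 to 4.03. A small ρ is conservative for a slope or change contrast, and the opposite for a time-averaged difference in means.

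**4. Callaway and Sant'Anna with the last pre-start month as the only base.** For an effect averaged over p post-start months, SE = 73 × √[0.95 × (1 + 1/p)] × 0.02387.

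| p | SE | MDD | Power at 2.4 |
|---|---|---|---|
| 6 | 1.834 | 5.9 | 26% |
| 12 | 1.767 | 5.7 | 27% |
| 30 | 1.726 | 5.6 | 28% |
| 59 | 1.712 | 5.6 | 29% |

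The base month dominates the variance, so extra post-start months barely help.

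**5. DID averaging all q pre-start months.** SE = 73 × √[0.95 × (1/q + 1/p)] × 0.02387.

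| q / p | SE | MDD | Power at 2.4 |
|---|---|---|---|
| 6 / 54 | 0.731 | 2.37 | 90.7% |
| 12 / 48 | 0.548 | 1.78 | 99.2% |
| 30 / 30 | 0.438 | 1.42 | above 99.9% |
| 48 / 12 | 0.548 | 1.78 | 99.2% |

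Steps 4 and 5 assume a common start. A simulation with staggered starts (4,000 runs) gave 26.9% and 99.9% respectively.

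**6. How firm the inputs are.** 244 × 300 × 60 = 4,392,000; the printed 8,784,000 is twice that. Reaching the printed total with 120 months gives a slope gap of 1.73; with 600 users per county, 1.71. Single-base-month power at 2.4 is then 28.8% or 50.3%. All figures above apply SD 73 to each person-month. If it is the SD of county values and the 244 counties are the units, the SEs become 12.9 (slope), 29.9 (single base month, p = 30) and 7.6 (30/30 DID), and two-sided power at 2.4 is about 5% to 6% in every case.

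**The case against.** The strongest reply is that the paragraph discloses its interaction test, that its arithmetic reproduces, and that a gap between group means at month 60 is still a difference between means. The first two points stand: this is not a miscalculation. The third makes the label ambiguous rather than correct, because the text never says that the gap refers to month 60 or that the average gap is half as large.

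A reader might infer that the planned DID has about 28% power at 2.4 rather than 90%. The documents do not support that. The 28% needs a single base month. The article permits a similar method and fixes no base period. It also plans a Bacon-Goodman decomposition, which presupposes a pooled two-way fixed-effects coefficient. With all pre-start months averaged, 2.4 is comfortably detectable on the same inputs. An article may leave base period and split to a fuller document, and their absence is not the complaint.

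It can also be said that month might enter the group-by-period term linearly, which would match the powered test. The article does not rule this out. But a straight divergence from month 1 across pre-start months contradicts the parallel pre-trends that the DID assumes, and one fitted only after program start has no pre-period to difference against.

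Finally, the slope reading is not the only route to 2.4: a pooled DID with a 6/54 or 54/6 split gives 2.37. No such split is stated, and the described interaction test favours the slope reading.

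**Conclusion.** The point holds in a limited form. The 2.4 is best read as the month-60 divergence of a linear slope-difference test, with an average gap of about 1.2, and should not be presented as a plain difference in means. The 90% is therefore not established for the Objective 2 DID. On the printed 300 users and 60 months, power at 2.4 runs from about 26% to 29% (single base month) to 99% or more (all pre-start months averaged, splits from 12/48 to 48/12), depending on a choice that the article leaves open.

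Neither end should replace the 90%. Both inherit the inconsistent observation total and the person-month use of a county-level SD. What is shown is that the published figure belongs to another test and that the answer is very sensitive to the estimator. The confidence expressed under Limitations therefore has no calculation behind it for the planned analysis.

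**What to change.** - In Power Calculation: Objective 2, describe 2.4 as the divergence reached at month 60 under a linear slope-difference model (average about 1.2).
- Replace the headline with a minimum detectable difference for the DID estimator actually chosen, for example by simulation from the 2016-2024 monthly panel already held. State the base period, the pre-start and post-start months and the county-level variance, and reconcile the observation total with its factors.
- Redo the state-level figure in the same way.
- Restate the data-sufficiency claim under Limitations to match.

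A baseline pooled over all pre-start months is an option where the planned pre-trend checks hold; it is not a required change, and it relies on parallel trends over the whole pre-period.

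The cost is a short simulation and a reworded paragraph, with no new data. The downside is that the stated detectable difference may become less favourable.

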#### Preliminary Findings Regarding PrEP Use Determination

We sought to determine levels of PrEP use in the third-party provider dataset (Symphony Health, an ICON plc Company, PatientSource®, January 1, 2016 to December 31, 2024). For prescriptions from aggregated datasets, a medication may sometimes be used for more than one purpose, so it is necessary to determine which prescriptions are intended for PrEP use. Informed by prior work in this area [43], we developed an algorithm to identify prescriptions for PrEP use (see Figure 3), with our algorithm foremost guided by published clinical guidance [44-50] and the availability of relevant data in the dataset. For this analysis, we extracted all prescription claims with approved PrEP medication names, that is, emtricitabine and tenofovir disoproxil fumarate (fluoro-thiacytidine [FTC]/TDF), emtricitabine and tenofovir alafenamide fumarate (FTC/TAF), and cabotegravir (CAB) (inclusion criteria 1), and then excluded the claims associated with either HIV treatment (ART) or postexposure prophylaxis (PEP). We first excluded any prescription claims that were part of a triple ARV regimen (exclusion criterion 1) and then excluded any prescription and procedure claims within 3 days of a PEP diagnosis (exclusion criterion 2). To further exclude prescription claims that were intended for HIV treatment, we incorporated relevant diagnosis data, a dataset of over 7 million HIV diagnosis claims and 60,000 PEP diagnosis claims. Medical conditions diagnosed by providers were provided in the dataset with *ICD-9-CM* or *ICD-10-CM* codes. While *ICD-10-CM* codes have replaced the *ICD-9-CM* codes since 2015 for billing purposes, some health systems may still be using *ICD-9-CM* codes. We extracted all codes related to HIV conditions (see Multimedia Appendix 3) and aggregated the number of HIV diagnoses based on the number of HIV condition-related codes for each patient. Given that for PrEP or PEP care HIV diagnoses can be mistakenly entered into the medical chart [51-53], we did not automatically exclude all persons with a single HIV diagnosis. Instead, we excluded (1) all claims for persons with two or more HIV diagnoses, (2) claims for persons with one HIV diagnosis and three or more periods of triple ARV regimen, and (3) claims for persons with no HIV diagnosis but with three or more periods of triple ARV regimen that indicate likely treatment (exclusion criterion 3). For persons with only a single HIV diagnosis and 2 or fewer triple ARV prescriptions, the triple ARV prescriptions could be for PEP, so nontriple therapy PrEP medication claims for these persons were eligible for inclusion. For individuals meeting exclusion criterion 3, the HIV diagnosis criteria, any claims for PrEP coming before the earlier of either the first HIV diagnosis or the first triple ARV regimen claim were not excluded (inclusion criteria 2). Last, we excluded the small number of claims that could represent entry errors or did not follow prescribing guidance (exclusion criterion 4): any claims for PrEP that did not reflect the standard drug strength, any claims for persons under the age of 12 years at the time of prescription, and claims for medications prior to their FDA approval—FTC/TAF prior to October 3, 2019, generic FTC/TDF prior to October 2, 2020, and CAB prior to December 20, 2021.

PrEP medications may be billed through either pharmacy or medical benefits, depending on how the medication is dispensed and the requirements of the insurance plan. Oral PrEP is typically filled at a pharmacy, and so it is captured under pharmacy claims within national aggregator datasets. In rare cases, oral PrEP can also be filled through medical benefits under the Healthcare Common Procedure Coding System (HCPCS) level two J codes, such as J0750 (FTC/TDF), J0751 (FTC/TAF), or unclassified drug codes (C9399 or J3490), with either FTC/TDF or FTC/TAF listed as the drug administered. LAI PrEP (ie, CAB) is administered in clinical settings and therefore reimbursed through medical benefits, which are captured as procedure claims using the HCPCS level two J codes such as J0739 (CAB), or unclassified drug codes (C9399 or J3490) with CAB listed as the drug administered. Depending on insurance coverage, LAI PrEP may be obtained via specialty pharmacies and covered under the pharmacy benefit. Although there is limited overlap of these datasets, we sought to ensure deduplication across PrEP claims across prescription and procedure claims datasets. For LAI PrEP, prescription and procedure claims occurring within 15 days of each other were considered as the same injection and deduplicated. A 15-day period was selected because it is less than the minimum clinical window of 1-month spacing for LAI PrEP [54]. For oral PrEP, prescription and procedure claims occurring on the same day or within a 3-day window were considered as the same prescribing event and deduplicated accordingly. We selected a 3-day window because some monthly patients can opt to refill their medications early, but we expect a small period of time to elapse before they refill.

**Figure 3 figure3:**
[figure not shown]
PrEP Epidemiology, Modeling, and Surveillance (PREMISE) research program of PrEP use determination algorithm flow diagram. The flow diagram shows the algorithm developed to identify eligible PrEP prescription and procedure claims from the national PrEP database from a third-party data provider, including the inclusion and exclusion criteria applied at each decision point, leading to the final PrEP prescription and procedure datasets. ARV: antiretroviral; CAB: cabotegravir; FDA: Food and Drug Administration; FTC: fluoro-thiacytidine; ICD-9-CM: International Classification of Diseases, Ninth Revision, Clinical Modification; ICD-10-CM: International Classification of Diseases, Tenth Revision, Clinical Modification; PEP: postexposure prophylaxis; PrEP: pre-exposure prophylaxis; TAF: tenofovir alafenamide fumarate; TDF: tenofovir disoproxil fumarate.

### Ethical Considerations

This study involves secondary data analysis of fully deidentified prescription claims, procedure claims, and diagnosis code data, as well as a survey of US health jurisdictions to gather information on PrEP-related funding and program implementation. There was no human subjects enrollment or interaction, and no collection or use of any personal identifiable information. As such, this study does not constitute human subjects research or clinical investigation as defined in the federal regulations and was not subjected to institutional review board (IRB) review [55]. Investigators completed a worksheet provided by the Emory IRB, documenting that IRB review was not required. The study claims data are accessed by Emory under a contract and data use agreement with a third-party provider that specifies appropriate storage and data security procedures. As is normative for this type of claims data, the contract does not allow for external sharing of line-level data by Emory. However, other investigators can access the data directly through the data provider, ICON plc.

## Results

### Preliminary Findings

From 2016 to 2024, there were more than 20 million claims of medications approved by the FDA for PrEP: FTC/TDF, FTC/TAF, and CAB (see Figure 4). From these prescriptions, we excluded about 6 million claims for coinciding periods that included triple ARV drug regimens (exclusion criterion 1). We then merged the diagnosis claims into the dataset to allow for further determination. We confirmed 11 million PrEP prescription claims that were connected to individuals who had no HIV diagnosis, no PEP diagnosis, and had never used a triple ARV regimen (Group 1 certified PrEP claims). For the remaining 3 million claims, we used clinical guidance for possible other uses of the drugs to determine whether a prescription was for PrEP (Group 2 certified PrEP claims) or for an alternative use. We determined 700,000 of these claims to be not for PrEP use: 6000 claims for PrEP medications that occurred within 3 days of a PEP diagnosis (exclusion criterion 2), 447,000 claims from individuals with 2 or more HIV diagnosis codes (exclusion criterion 3), 247,000 claims from individuals with only one HIV diagnosis, and 3 or more claims for triple ARV regimens (exclusion criterion 3). About 25,000 claims for PrEP medications occurred prior to FDA medication approval, 500 claims for individuals under the age of 12 years at the time of prescription, and 26,000 claims did not reflect standard PrEP drug strengths (exclusion criterion 4). This led to a final prescription dataset with over 1 million cumulative patients having initiated PrEP and over 13 million separate PrEP prescriptions.

**Figure 4 figure4:**
[figure not shown]
PrEP Epidemiology, Modeling, and Surveillance (PREMISE) research program filtering process for identifying and extracting valid PrEP prescription claims. This figure illustrates the determination of PrEP prescriptions; after initial analysis of prescription claims, diagnosis claims inform exclusion, allowing us to identify the total number of PrEP prescription claims and patients. From 2016 to 2024, there were 20,394,619 prescription claims for FTC/TDF, FTC/TAF, and cabotegravir. We excluded 5,997,614 prescription claims identified to be part of the triple ARV regimen (exclusion 1), 6354 prescription claims occurring within 3 days of PEP diagnosis identified to be for PEP (exclusion 2), 694,379 prescription claims identified to be for treatment (exclusion 3), and 51,293 prescription claims identified to be erroneous entries or not following approved PrEP prescribing guidance (exclusion 4). The final prescription dataset contained 13,644,979 PrEP prescription claims representing 1,079,942 unique patients. ARV: antiretroviral; FTC: fluoro-thiacytidine; PEP: postexposure prophylaxis; PrEP: pre-exposure prophylaxis; TAF: tenofovir alafenamide fumarate; TDF: tenofovir disoproxil fumarate.

For medical benefits claims, there were about 34,000 procedure claims for PrEP provided in a clinical setting (see Figure 5). From these procedure claims, we excluded about 600 claims for coinciding periods that included triple ARV drug regimens (exclusion criterion 1). Using the same diagnosis claims dataset as described above, we confirmed 25,000 PrEP procedure claims for individuals who had no HIV diagnosis, had no PEP diagnosis, and had never used a triple ARV regimen (Group 1 certified PrEP claims). For the remaining 9000 claims, using the same clinical guidance as described above to determine whether a procedure was for PrEP (Group 2 certified PrEP claims), we determined 2200 of these claims to be not for PrEP use: 1670 claims from individuals with 2 or more HIV diagnosis codes (exclusion criterion 3), with the remaining claims from individuals with only 1 HIV diagnosis and 3 or more claims for triple ARV regimens (exclusion criterion 3), or PrEP medications that occurred within 3 days of a PEP diagnosis (exclusion criterion 2). About 9000 procedure claims for PrEP were duplicates. Under exclusion criterion 4, there was 1 claim for an individual under the age of 12 years at the time of procedure and about 100 claims for LAI PrEP with the drug name “cabotegravir” listed but an incorrect HCPCS level two J code. This led to a final procedure dataset with over 6000 cumulative patients having initiated PrEP through medical benefits with about 22,500 procedure claims for LAI PrEP and about 400 procedure claims for oral PrEP.

**Figure 5 figure5:**
[figure not shown]
PrEP Epidemiology, Modeling, and Surveillance (PREMISE) research program filtering process for identifying and extracting valid PrEP procedure claims. This figure illustrates the process of determining PrEP procedures from the dataset, following the exclusion criteria as described in the main text. After initial analysis with procedure claims, we add diagnosis claims to further exclude procedures anticipated to not be for PrEP, showing the final number of PrEP procedure claims and patients retained. From 2016 to 2024, there were 34,525 procedure claims for FTC/TDF, FTC/TAF, and cabotegravir. We excluded 564 procedure claims identified to be part of the triple ARV regimen (exclusion 1), 2 procedure claims occurring within 3 days of PEP diagnosis identified to be for PEP (exclusion 2), 2244 procedure claims identified to be for treatment (exclusion 3), and 98 procedure claims identified to be erroneous entries or not following approved PrEP prescribing guidance (exclusion 4). The final procedure dataset contained 22,910 PrEP procedure claims representing 6196 unique patients. ARV: antiretroviral; FTC: fluoro-thiacytidine; HCPCS: Healthcare Common Procedure Coding System; PEP: postexposure prophylaxis; PrEP: pre-exposure prophylaxis; TAF: tenofovir alafenamide fumarate; TDF: tenofovir disoproxil fumarate.

By developing an algorithm to determine PrEP use from other prescribing of ARV medication, this early analysis provides outcome data for all subsequent components of the PREMISE project. For objective 1, these data will be used to inform our descriptive and longitudinal analyses of changes in PrEP use over time. To accomplish objective 2, the data will be used as an outcome variable, allowing for the determination of the impact of PrEP policies and programs. To guide objective 3, these data will be used to inform the modeling of the future impacts and cost-effectiveness of different programs and policies.

